**Lay Summary**

In 2014, Li et al published a paper reporting evidence to suggest that the use of the phosphodiesterase type-5 (PDE5) inhibitor, sildenafil, typically used to treat erectile dysfunction, increased the risk of a type of skin cancer known as malignant melanoma, in a US-based cohort of male health professionals. This was the first epidemiological evidence to suggest an association between a PDE5 inhibitor and melanoma and as yet, has not been replicated using another data source. As NHS restrictions regarding the prescription of PDE5 inhibitors have recently been relaxed, meaning the drugs are more readily available, this finding could have important public health implications. We aim to examine the association between PDE5 inhibitors and the risk of incident melanoma among men in the UK using data from CPRD.

To examine the association between PDE5 inhibitors and melanoma we will initially compare the risk of melanoma in individuals that have ever been exposed to a PDE5 inhibitor to similar individuals that have never been exposed to a PDE5 inhibitor. We will then go on to assess the effect of the cumulative numbers of PDE5 prescriptions on the risk of incident melanoma.

**Background**

Malignant melanoma is the 6^th^ most common cancer in males the UK [1]. In 2011, the age standardised incidence rate was 17.5 (95% CI: 17.1, 18.0) cases per 100,000 men [1] and rates are significantly higher in the south and south west areas of the UK [2]. It is generally accepted that the main risk factor of malignant melanoma is exposure to UV radiation from both sun exposure and tanning beds [3].

The PDE5 inhibitor, sildenafil (marketed as Viagra), is principally used in the treatment of erectile dysfunction (ED) [4]. Li et al recently reported epidemiological evidence to suggest an increased risk of melanoma due to sildenafil use in a US based cohort of health professionals, using self-reported data [5]. However, as yet, this observation has not been replicated using another data source.

Until recently, prescription of PDE5 inhibitors on the NHS was restricted to men presenting with both ED and one of a number of pre specified diagnoses, including diabetes, renal failure and severe distress [6]. On 21^st^ June 2013, Pfizer’s patent for sildenafil expired in the UK, opening the window for other manufacturers to sell generic versions at a lower cost. Due to this change in the market, generic sildenafil has recently become available on the NHS to all men presenting with ED. The increased availability of the drug on the NHS has the potential to considerably inflate demand.

As the association found by Li et al is novel, this study will aim examine the association between both sildenafil and other PDE5 inhibitors used for erectile dysfunction and the risk of incident melanoma among men in the UK CPRD.

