**Study Population**

We will identify all male patients over the age of 18 with an incident exposure to a PDE5 inhibitor from 1^st^ July 1999 to 1^st^ August 2014 inclusive. The reasoning behind the proposed study period is that the restrictions regarding the prior diagnoses required to receive a PDE5 inhibitor prescription were imposed on 1^st^ July 1999, and restrictions for generic sildenafil were lifted on 1^st^ August 2014, after Pfizer’s sildenafil patent expired on 21^st^ June 2013. Follow up will begin at the date of first PDE5 inhibitor prescription (hereafter the “index date”). Exposed patients will matched to up to four controls on age at first prescription (within 3 years in either direction), GP practice, diabetes status, and their index date will be the same as their matched case’s. All matching variables will be measured at the index date. Patients with any cancer diagnoses prior to the index date will be excluded. Individuals selected as controls may later go on to start a PDE5 inhibitor; in this situation they will be censored as a control at the time of starting a PDE5 inhibitor, and they will contribute separately as an exposed patient from that time point (with their own matched controls).

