Age, GP practice, diabetes status and calendar time are matching variables. Our models will also be adjusted for the following potential confounders evaluated at beginning of follow up:

- Smoking status (never-smoker, current smoker, ex-smoker)
- BMI (underweight, normal, overweight, obese)
- Alcohol status (never-drinker, current drinker, ex-drinker)
- Index of multiple deprivation score

*Interaction*

We will fit interaction terms to explore possible effect modification between exposure to a PDE5 inhibitor and age, smoking status and index of multiple deprivation score.

*Sensitivity analysis*

As a sensitivity analysis we will exclude the first 12 months of follow up after index date in both exposed and unexposed patients. This is to decrease the chance of reverse causality, whereby undiagnosed melanoma cancers cause ED and hence the need for a PDE5 inhibitor prescription.

We will also conduct an analysis restricted to patients diagnosed with diabetes as previous restrictions mean all patients diagnosed with diabetes were definitely eligible for a PDE5 prescription.

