**CHANGES FROM THE PROTOCOL AND EXPLANATION**

We added an extra exclusion criteria: men with no consultation in the year prior to the index date were excluded from the study. This is because we initially discovered a large discrepancy in the proportion of non-consulting patients between the exposed and unexposed groups, with the unexposed much more likely to be non-consulters, implying a potential for substantial differences in ascertainment of outcomes, and therefore bias. All analyses were otherwise carried out as pre-specified, but we conducted some further analyses to assess causality and exclude bias, as follows:

1. We added an extra secondary analysis to investigate changes in the association between PDE5 use and melanoma by time since first prescription date. This was to further explore whether patterns of effects were consistent with causality.

2. We investigated interaction by practice region, as well as by the pre-specified potential effect modifiers. This was because of an apparent important role for sun exposure; the climate in the southern UK is generally warmer with more hours of sunshine than in the northern part of the country.

3. We added three negative control outcomes (basal cell carcinoma, solar keratosis, colorectal cancer) as a way of excluding bias. No causal effects of PDE5 inhibitor use were postulated for these outcomes. The specific outcomes were chosen to incorporate one non-melanoma skin malignancy, one non-malignant skin condition, and one condition unrelated to skin.

4. We conducted a post-hoc analysis to relate PDE5 exposure to prior solar keratosis, in order to assess possible confounding by sun exposure.

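### Diabetes is the only NHS eligibility diagnosis matched or adjusted for, so the ever-exposed hazard ratio may be confounded by the others

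*Combined protocol and SAP*

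**What the plan says.** The Background describes the prescribing rule: until recently, NHS supply was "restricted to men presenting with both ED and one of a number of pre specified diagnoses, including diabetes, renal failure and severe distress". The Study Population section explains the accrual window (1 July 1999 to 1 August 2014) by that rule. Its start is explained by the fact that "the restrictions regarding the prior diagnoses required to receive a PDE5 inhibitor prescription were imposed on 1^st^ July 1999", and its end is the date on which they were lifted for generic sildenafil.

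Exposed men are "matched to up to four controls on age at first prescription (within 3 years in either direction), GP practice, diabetes status", and controls share the index date. The Confounding paragraph of the Statistical/analysis plan repeats this: "Age, GP practice, diabetes status and calendar time are matching variables". It continues: "Our models will also be adjusted for the following potential confounders evaluated at beginning of follow up". The covariates that follow are smoking, BMI, alcohol and the deprivation score. The Poisson model for absolute risk uses the same covariates plus time since index date.

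Three other provisions bear on the point:

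- The Sensitivity analysis paragraph plans an analysis in diabetic men only, because "previous restrictions mean all patients diagnosed with diabetes were definitely eligible for a PDE5 prescription".
- The section on changes from the protocol reports that "men with no consultation in the year prior to the index date were excluded from the study".
- The same section says: "We added three negative control outcomes (basal cell carcinoma, solar keratosis, colorectal cancer) as a way of excluding bias".

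**The concern.** Under the rule as the Background describes it, a man without diabetes needed some other listed diagnosis to receive the drug on the NHS. His controls are also non-diabetic, by matching, but nothing requires them to have any listed diagnosis. Within non-diabetic matched sets, the prescribing rule itself therefore makes renal failure, severe distress and the other listed diagnoses more common in the exposed man than in his controls.

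If those diagnoses are related to melanoma, or to the chance that a melanoma is found and coded, part of the ever-exposed hazard ratio (Aim 1) would belong to them and not to the drug. The absolute risks would carry the same error, because the Poisson model has the same covariates. Under Aim 2, each prescription category compared with non-users could be shifted in the same way.

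Detection is the more concrete route. The section on changes from the protocol reports that exposed and unexposed men differed markedly in how often they consulted, and it treats this as a threat to outcome ascertainment. Long-term diagnoses are a plausible source of extra medical contact.

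**Working it through.** **Step 1. Where each named diagnosis is handled**

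| Diagnosis named in the Background | Matched | In adjusted model | In descriptive variables | In Limitations |
|---|---|---|---|---|
| Diabetes | yes | through matching | yes | no |
| Renal failure | no | no | no | no |
| Severe distress | no | no | no | no |
| Others on the list (not named) | no | no | no | no |

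**Step 2. The plan's yardstick.** The Sample size section gives 80% power at an effect of about 1.18, with 179,298 exposed men matched 1:1 and a melanoma proportion of 0.27%. A two-sided 5% comparison of two proportions gives 76.6% power at 1.18 if 0.27% is the control risk, and 69.6% if it is the exposed risk. The effect detectable with 80% power is 1.188 or 1.208 respectively. The first is close to the stated figure, and the gap does not bear on this point. With a full 1:4 match, power at 1.18 is 88% to 93%. I use 1.18 only to give a sense of scale.

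**Step 3. Size of a possible bias.** For one unmeasured binary factor in non-diabetic sets:

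B = [1 + P1(RR − 1)] / [1 + P0(RR − 1)]

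P1 and P0 are the proportions of non-diabetic exposed men and of their controls who have a non-diabetes listed diagnosis. RR is the association of that diagnosis with recorded melanoma. Diabetic sets are taken as balanced. If a share f of exposed men is diabetic, the overall spurious hazard ratio is approximately B^(1 − f).

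None of these inputs is in the documents. Assumed ranges: f 20% to 40%, P1 50% to 100%, P0 5% to 20%, true hazard ratio 1.

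Worked corners at RR 1.5:

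- Smallest: P1 = 0.5, P0 = 0.2, f = 0.4. B = 1.25/1.10 = 1.136, and 1.136^0.6 = 1.08.
- Largest: P1 = 1, P0 = 0.05, f = 0.2. B = 1.50/1.025 = 1.463, and 1.463^0.8 = 1.36.

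| RR assumed | Spurious hazard ratio |
|---|---|
| 0.8 | 0.84 to 0.96 |
| 1.0 | 1.00 |
| 1.2 | 1.03 to 1.15 |
| 1.5 | 1.08 to 1.36 |
| 2.0 | 1.14 to 1.67 |

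Setting B = 1.18 gives RR = 1 + 0.18/(P1 − 1.18 P0). Within non-diabetic sets, an RR of 1.19 to 1.24 is enough if P1 is 100%, and 1.41 to 1.68 if P1 is 50%.

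**Step 4. Lower prevalences.** If the rule was followed less strictly, the same formula can be applied to all exposed men and all controls:

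| Prevalence, exposed / controls (assumed) | RR 1.2 | RR 1.5 | RR 2 |
|---|---|---|---|
| 10% / 2% | 1.02 | 1.04 | 1.08 |
| 20% / 5% | 1.03 | 1.07 | 1.14 |
| 30% / 5% | 1.05 | 1.12 | 1.24 |

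**Step 5. How strong a check the diabetes-only analysis is.** With 1:4 matching and 0.27% in exposed men, power at 1.18 is 31%, 42% and 53% if 20%, 30% and 40% of exposed men are diabetic (assumed shares). The effects detectable with 80% power are 1.404, 1.315 and 1.265.

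**The case against.** The strongest reply is that imbalance is not confounding. The other listed diagnoses must also affect melanoma or its recording, and nothing in the documents says that renal failure or severe distress does. This stands. A reader might infer that the hazard ratio is known to mix the drug with these diagnoses, and the text does not support that. The bias is nil at RR 1 and downward below 1.

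A reader might also infer that the window was chosen in order to enrich the exposed group. The Study Population section says only that the window follows the dates of the restriction.

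Nor should one read an artefactual dose-response into Aim 2. The rule applied to a man with one prescription as much as to a man with more than 20, so it does not by itself create a gradient across categories.

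The authors did respond to parts of the problem. In diabetic men, exposed and controls alike were eligible, so that analysis asks directly whether the estimate survives without eligibility-driven selection. The consultation exclusion and the negative control outcomes probe the medical-contact route. All this deserves credit, but each has a limit. The diabetes-only analysis is probably imprecise and says nothing about non-diabetic men. The exclusion removes men with no contact but does not equalise contact or diagnoses above one consultation. Negative controls can signal bias but do not remove it from the melanoma estimate.

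Finally, adjustment has its own hazards. If the rule was followed closely, nearly every non-diabetic exposed man has a listed diagnosis, and the adjusted estimate leans on the minority of controls who have one too. If severe distress is poorly coded, the misclassification may differ by exposure. This also stands, and it argues for a sensitivity analysis and against changing the primary model.

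**Conclusion.** The point holds as a possible confounding that the plan leaves open. Accrual coincides with a rule requiring ED plus a listed diagnosis, and only one listed diagnosis, diabetes, is controlled. The ever-exposed hazard ratio and the absolute risks may be biased by the rest, if these relate to melanoma or its detection. The same shift could apply to each cumulative category against non-users.

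Neither direction nor size can be taken from the documents. The illustrative ranges rest on assumed prevalences, an assumed diabetic share, an assumed risk ratio, a single binary factor and balanced diabetic sets. They show that a modest association could matter next to an effect of about 1.18 if the rule was followed closely, and that the bias is small if prevalences are low or the association is weak. This is a reason to look at data already held. It is not a reason to discount the primary result.

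**What to change.** From the CPRD records, derive an indicator at the index date for each non-diabetes eligibility diagnosis. The Background names renal failure and severe distress; the rest should be taken from the NHS list in force over the study period. Then:

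1. Tabulate the indicators by exposure group in the descriptive analyses.
2. Pre-specify a sensitivity analysis that adds them to the adjusted Cox model, and report the hazard ratio with and without them.
3. Name the issue under Limitations, including that its direction is unknown.

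If this is run after the main results are known, label it as an added analysis, as the section on changes from the protocol does for others.

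The cost is some extra code lists on data already held. Precision will fall if the indicators track exposure closely. Adjustment will be only partial, and possibly differential between groups, where coding is incomplete, notably for severe distress. The primary covariate set need not change.

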**Objective, specific aims and rationale**

*Objective*

To assess the effect of PDE5 inhibitors on the risk malignant melanoma in men in the UK

*Aims*

1. Assess the effect of ever using a PDE5 inhibitor on the risk of malignant melanoma
2. Assess the cumulative effect of number of PDE5 inhibitor prescriptions on the risk of malignant melanoma
3. Investigate whether individual-level characteristics modify the association between PDE5 inhibitors and malignant melanoma risk

*Rationale*

There has previously been only one study in the USA that assessed this association and found PDE5 inhibitors to increase the risk of malignant melanoma; this received considerable attention, but the finding has not since been replicated. We therefore believe it will be beneficial to explore whether this association can be replicated in a separate population.

**Study Type**

Hypothesis testing with the null hypothesis that PDE5 inhibitors have no effect on the risk of malignant melanoma in men the UK.

**Study Design**

Matched cohort study using CPRD

**Linked Data**

Patient-level index of multiple deprivation data are required to assess for confounding as it is thought that a combination of socio-demographic status and geographical location can be used as a proxy for levels of sun exposure. Since this is only available for patients in the linkage scheme, we propose to use practice-level index of multiple deprivation for the remainder of patients (rescaled to be on the same scale as the patient level scores, using observations where both are available). We have used this strategy successfully in previous CPRD studies.

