**Statistical/analysis plan**

Within the cohort, a patient’s observation time will begin at the index date and will end when one of the following occur: incident malignant melanoma, at diagnosis of a cancer other than malignant melanoma, death, transfer out of CPRD network, prescription of a PDE5 inhibitor (for unexposed controls), or end of follow up. The following analyses will be carried out using incident malignant melanoma as the primary outcome.

*Descriptive analyses*

Prior to exploring the relationship between PDE5 inhibitors and malignant melanoma, we will firstly describe the distribution of exposed and unexposed within the following variables: age, ever prescribed a PDE5 inhibitor, GP practice region (North East, North West, Yorkshire & the Humber, East Midlands, West Midlands, East of England, South West, South Central, London, South East Coast, Northern Ireland, Scotland, Wales), diabetes status, smoking status (non-smoker, current smoker, ex-smoker), BMI (underweight, normal, overweight/obese), alcohol status (non-drinker, current drinker, ex-drinker), index of multiple deprivation score.

*Ever exposed vs. never exposed to a PDE5 inhibitor*

Crude incidence ratios will firstly be calculated. The main exposure variable will then be included in an unadjusted and adjusted Cox regression model (see “Confounding” below), stratified by matched set to account for the matching. The primary outcome will be a diagnosis of incident melanoma and patients will be censored at diagnosis of any other cancer, death, transfer out of the CPRD network, or on 21^st^ June 2013 (end of follow up). Hazard ratios and 95% confidence intervals will be estimated, comparing the rate of incident melanoma between patients who have ever been prescribed a PDE5 inhibitor and patients that have never been prescribed a PDE5 inhibitor. We will also calculate changes in absolute risk of melanoma by obtaining predictions from a Poisson model with the same covariates as our main Cox model, plus time since index date (time-updated).

*Cumulative duration of exposure*

Unadjusted and adjusted Cox regression models will then be re-run using a time updated variable capturing the cumulative number of PDE5 inhibitor prescriptions in place of the ever exposed variable. Hazard ratios and 95% confidence intervals will again be estimated.

*Confounding*

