**Limitations**

*Missing data*

Although there is known missingness in the smoking and alcohol status and BMI variables, this is minimal. Initial feasibility analyses using a CPRD random sample show that 2.3% and 1% of patients prescribed a PDE5 inhibitor have missing data for alcohol status and smoking status respectively. We plan to conduct a complete case analysis, which relies on the assumption that the probability of these data being missing is independent of melanoma risk, conditional on covariates [7]; given the small amount of missing data, any violation of the assumption is unlikely to importantly affect the results.

*Lack of data on UV Exposure*

UV exposure is a strong risk factor for malignant melanoma, though it is unclear as to whether UV exposure is likely to be associated with PDE5 inhibitor use and therefore a potential confounder. As data on patient level UV exposure are unavailable, we will match on GP practice as we believe patients from the same practice will have similar sun exposures whilst at home due to geographical location, though a limitation is that it will be impossible for us to take account of amount of time spent outdoors. We will also adjust for index of multiple deprivation score as we believe this will to some extent act as a proxy for amount of travel abroad.

*Sale of PDE5 inhibitors without a prescription*

There is a high volume of PDE5 inhibitors, especially sildenafil (marked as Viagra), sold illegally. It is therefore possible that patients could obtain medication without a prescription resulting in exposure status misclassification. If this is the case, it would result in an underestimation of the true effect size.

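### In practice-matched sets where every man carries the practice-level deprivation score, that score cancels from the set-stratified Cox model, so within-practice confounding by deprivation is not adjusted for there.

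*Combined protocol and SAP*

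**What the plan says.** Four parts of the combined protocol and SAP bear on this point.

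- **Linked Data.** The reason for wanting the individual score is explicit: "Patient-level index of multiple deprivation data are required to assess for confounding". It exists only for men in the linkage scheme. For the others, "we propose to use practice-level index of multiple deprivation for the remainder of patients", and the substituted score is to be "rescaled to be on the same scale as the patient level scores, using observations where both are available".
- **Study Population.** "Exposed patients will matched to up to four controls on age at first prescription (within 3 years in either direction), GP practice, diabetes status". Controls also take the index date of their exposed man.
- **Statistical/analysis plan.** The main Cox model is "stratified by matched set to account for the matching". Under Confounding, the covariates are introduced with "Our models will also be adjusted for the following potential confounders evaluated at beginning of follow up", and IMD is on the list with smoking, BMI and alcohol.
- **Limitations, Lack of data on UV Exposure.** Practice matching stands in for shared location. IMD is then given a further job: "We will also adjust for index of multiple deprivation score as we believe this will to some extent act as a proxy" for travel abroad.

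The documents do not say what share of men is unlinked, or whether linkage goes by whole practice or by individual. They do not note that a practice-level score is constant within a practice-matched set, and they plan no analysis restricted to linked men.

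**The concern.** Each of these choices is reasonable alone; the difficulty lies in combining them. Matching on practice and stratifying by set already remove deprivation differences between practices. An IMD term in the Cox model can therefore add only control for differences between men of the same practice. A practice-level score carries no information on those differences.

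If exposed men are more or less deprived than their same-practice controls, and deprivation tracks travel and sun exposure as the Limitations section supposes, that confounding stays in the HR from every wholly unlinked set. A reader told that the model adjusts for IMD would reasonably take this to mean individual-level adjustment throughout the cohort.

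**Working it through.** The plan states no figure to reproduce here. The core of the point is algebraic; the arithmetic only illustrates its size.

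**Step 1: cancellation.** Let x be exposure and d be IMD, with log hazard ratios b and g. In a Cox model stratified by set s, an event in man i contributes

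exp(b·x_i + g·d_i) / Σ_j exp(b·x_j + g·d_j), with j running over the men of set s still at risk.

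If d_j = d_s for every member, exp(g·d_s) factors out of numerator and denominator, leaving exp(b·x_i) / Σ_j exp(b·x_j). The set says nothing about g, and its contribution to b is the same with or without IMD. Rescaling does not help, because any function of a practice score is still one value per practice. Baseline measurement does not help either, because set members share an index date.

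**Step 2: numerical check.** Assumed values: true HR 1.00, IMD log-HR −0.3 per unit, exposed men 0.3 units less deprived than same-practice controls, 400,000 sets of one exposed man and four controls, one event per set. The expected unadjusted HR is about exp(0.3 × 0.3) = exp(0.09) = 1.094.

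| Linkage | HR without IMD | HR with IMD |
|---|---|---|
| All men linked | 1.088 | 0.996 |
| No man linked | 1.092 | 1.092 (information on g = 0) |
| Half of practices wholly unlinked | 1.093 | 1.046 |
| – unlinked sets only | 1.097 | 1.097 |
| – linked sets only | not computed | 0.995 |
| Random by man, 50% linked | 1.099 | 1.051 |
| Random by man, 90% linked | 1.088 | 1.005 |

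The term is exactly null in wholly unlinked sets. In mixed sets it acts in part, because one man's own score is set against another man's practice average.

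**Step 3: size when linkage goes by practice.** Let u be the unlinked share of sets and C the unadjusted HR produced by within-practice confounding when the true HR is 1. Linked sets centre on log-HR 0 and unlinked sets on log C. With similar information per set,

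residual log-HR ≈ u × log C, so residual HR ≈ C^u.

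The half-unlinked row agrees: 1.093^0.5 = 1.045, against 1.046 simulated.

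| u | C = 1.05 (log C = 0.0488) | C = 1.15 (log C = 0.1398) |
|---|---|---|
| 25% | exp(0.0122) = 1.012 | exp(0.0349) = 1.036 |
| 50% | exp(0.0244) = 1.025 | exp(0.0699) = 1.072 |
| 75% | exp(0.0366) = 1.037 | exp(0.1048) = 1.111 |

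A separate simulation (600,000 sets of 1:4, six replicates, unadjusted HR 1.152) gave 1.002, 1.036, 1.074 and 1.114 at 0%, 25%, 50% and 75% unlinked.

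**Step 4: scale.** The Sample size section puts the detectable effect at about 1.18 with 1:1 matching; log 1.18 = 0.1655. On the log scale, the residuals in the table run from 0.0122/0.1655 = 7% to 0.1048/0.1655 = 63% of that effect.

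**The case against.** The strongest reply concedes the algebra and disputes its weight.

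- **The inputs are unknown.** The unlinked share and the strength of confounding are both assumptions. If few sets are unlinked, or deprivation within a practice is barely related to PDE5 inhibitor use, little bias remains. This stands, and it is why only a range can be given.
- **Practice matching already does much of the work.** It controls between-practice deprivation in every set, and the Limitations section names it as the response to missing UV data, with IMD as an addition. That section also calls it unclear whether UV exposure is related to PDE5 inhibitor use. This stands: only the within-practice component is lost.
- **IMD is a partial proxy.** The plan claims no more than that, so even full linkage would not remove confounding by sun exposure. The return to about 1.00 with full linkage occurs because the simulations make IMD the whole confounder.
- **Sun-exposure checks were added.** The section on changes from the protocol describes negative control outcomes, including basal cell carcinoma and solar keratosis, and a post-hoc analysis of prior solar keratosis. These can reveal residual confounding, but they do not restore the missing adjustment.
- **The substitution does no harm in wholly unlinked sets.** It keeps those men in a complete-case analysis and leaves their matched comparison unchanged. This also stands, and it is a reason to keep the main model.

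The Linked Data section adds that the strategy has worked in previous studies. It does not say whether those studies matched on practice and stratified by set, so this does not answer the point.

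A reader might infer that the IMD adjustment is empty throughout, or that its coefficient rests on linked men alone. The documents do not support either reading. Fully linked sets are adjusted as intended. If mixed sets exist, practice-level values enter their risk-set comparisons and help to determine the coefficient.

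**Conclusion.** The point holds for the main Cox model. In sets where all men carry the practice-level score, deprivation is controlled only through practice matching, and the within-practice adjustment that patient-level IMD was meant to provide is absent. In mixed sets, if there are any, it is partial.

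For 25% to 75% of sets unlinked, the illustrative residual HR is about 1.01 to 1.04 if within-practice confounding gives an unadjusted HR of 1.05, and about 1.04 to 1.11 if it gives 1.15. These figures assume a true HR of 1.00, linkage by practice, equal confounding and information in linked and unlinked sets, and confounding that IMD captures in full. They show what could happen and do not estimate bias in this study.

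The point does not extend to the exposure-by-IMD interaction, because the product term still varies within a set. Nor does it apply to the Poisson model for absolute risk if that model is not stratified by set, which the plan does not state. It would also be too strong to say that the main result is invalid: the documents show neither a large unlinked share nor strong within-practice confounding. What the point limits is the claim that can be made about deprivation adjustment.

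**What to change.** Keep the main model and all men as planned. Then:

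1. Report the share of matched sets that are fully linked, mixed and wholly unlinked for IMD, and say whether linkage goes by practice or by man.
2. Add a sensitivity analysis in sets where the exposed man and at least one control have patient-level IMD, dropping unlinked members. Show the HR with and without IMD on the same men.
3. Base any claim of individual-level deprivation adjustment on that analysis. State that the other sets are adjusted for deprivation only through practice matching.

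Removing the practice-level score from the main model is not advised: IMD would then be missing for unlinked men, and the complete-case rule under Missing data could exclude them.

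The cost is one additional model comparison and some wording, with no new data. The downside is a wider interval in the linked subset. The section on changes from the protocol reports the analyses as done, and this one can be added to them as a labelled sensitivity analysis.
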